#### Secondary Hypotheses

Our secondary hypotheses are that the e-Counseling + Usual Care arm will be associated with significant improvement in the quality of life, adherence to self-care, and psychological adjustment from baseline to 4- and 12-month assessments. These outcomes will be measured using the following objective and validated indices: (1) the KCCQ (≥5 points increase in the summary score at the 4-month assessment) for quality of life, (2) the Canadian version of the Diet History Questionnaire II (DHQ II) [40] for diet habits, (3) the mean 4-day step count (as measured by accelerometry) [41,42] and the Physical Activity Scale for the Elderly (PASE) questionnaire [43] for physical activity level, (4) the medication possession ratio (MPR) [20] for medication adherence, (5) the generalized anxiety disorder (GAD-7) scale [44] and Patient Health Questionnaire (PHQ-9) [45] for anxiety and depressive symptoms, respectively, (6) the Perceived Stress Scale (PSS) [46] for stress level, and (7) Prochaska’s algorithm [47] for readiness to change self-care behaviors.

In addition, we hypothesize that the e-Counseling + usual care group will perform better than the Control groups at the 12-month assessment on the following prognostic measures of cardiovascular functioning: (1) increased exercise capacity as measured by the 6-minute walk test (6MWT) [48], (2) increased vagal-heart rate modulation [44,45] as measured by electrocardiography (ECG), (3) decreased values of the Seattle Heart Failure Model (SHFM) [49-51], N-terminal pro-brain natriuretic peptide (NT-proBNP) [52,53], high sensitivity C-reactive protein (hsCRP) [52,54], and (4) increased VO_2_ peak [55] during cardiopulmonary exercise testing.

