Autonomic nervous system function of the subjects will be assessed using heart rate variability. A 10-minute recording will be collected using a three-lead ECG. The data will be sampled at 1000 Hz using LabView (version 7.1, National Instruments). A custom heart rate variability software will be used to analyze RR interval data using a fast Fourier transformation to obtain low frequency (0.04-0.15 Hz) and high frequency (0.15-0.50 Hz) spectral components. Only the Toronto sample will be asked to provide an ECG recording at baseline and 12-month intervals.

Peak aerobic power (VO_2_ peak, oxygen consumption) and the VE/VCO_2_ (rate of elimination of carbon dioxide) slope will be used to assess exercise capacity of the subjects at the baseline and 12-month intervals. The VO_2_ peak has prognostic value [87]. It is associated with the quality of life [88], and it is sensitive to change following home-based training with telehealth in CHF patients [55]. We will be collecting this information on the subjects through medical chart review.

The SHFM provides a risk estimate that has been validated among patients with CHF [49-51]. It is derived from prognostic variables (diuretic dose/kg, systolic blood pressure, percent lymphocytes, haemoglobin, etiology, ejection fraction, cholesterol, uric acid, allopurinol, serum sodium, statin, NYHA class, age, and sex) that are easily obtained from medical charts. We will review the medical charts of the subjects to extract values for these abovementioned variables at the baseline and 12-month intervals. These will then be inserted into a freely available algorithm on the Internet. The generated SHFM score will be used in our analyses.

The brain natriuretic peptide (BNP) is a neurohormone that is synthesized in and secreted from the ventricular myocardium in response to elevated ventricular wall tension and stretch, and from the activation of the sympathetic and renin-angiotensin systems. BNP is increased in patients with CHF [89], and it correlates with risk for all-cause, cardiac, and pump-failure mortality. Proinflammatory hsCRP is elevated in CHF as the disease progresses [52,54]. We will extract these data, if available, from the medical charts of subjects at the baseline and 12-month assessments.

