#### Statistical Analysis

This trial will use a 2 parallel-group design with 3 repeated assessments at baseline, 4-, and 12-months. A generalized mixed model (GMM) will evaluate the primary outcome, which is a binary code of whether the 12-month KCCQ [39] increases ≥5 points [38]. Predictors will include baseline KCCQ, age, sex, body mass index, and Group (e-Counseling vs Control). The primary outcome will be coded as a “failure” in the event of CHF hospitalization or mortality, but not for “elective” medical procedures (eg, cardiac resynchronization therapy). GMM with repeated measures will assess binary secondary outcomes across 4- and 12-month intervals (eg, KCCQ and smoking status). This analysis is optimal as it adjusts for serial correlations across repeated measures and between individual subjects in each group. Predictors will include baseline KCCQ, age, sex, body mass index, time (4- vs 12- month assessment interval), and Group (e-Counseling vs Control). Significant interactions or main effects will be followed by Bonferroni post hoc tests for significance, *P*<.05, 2-sided. Data missing at random will be handled by multiple imputations. For continuous secondary outcomes, linear mixed models (LMM) [94] for repeated measures with a random intercept will assess whether within-subject improvement across 4- and 12-month intervals is independently associated with our e-Counseling protocol. This analysis adjusts for serial correlations across repeated measures and between subjects in each Group. Predictors will include the baseline dependent variable, age, sex, body mass index, time (4- vs 12-month assessment interval), and Group (e-Counseling vs Control). LMM with a random intercept will also evaluate whether e-Counseling vs Control demonstrates improvement at the 12-month interval in VO_2_ peak, NT-proBNP, hsCRP, and the SHFM.

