## Abbreviations

6MWT: 6-minute walk test
BNP: brain natriuretic peptide
CHF: chronic heart failure
CHF-CePPORT: Canadian e-Platform to Promote Behavioral Self-Management in Chronic Heart Failure
COHRT: Community Outreach Heart Health and Risk Reduction Trial
CONSORT: Consolidated Standards of Reporting Trials
DHQ II: Diet History Questionnaire II
ECG: electrocardiography
GAD-7: generalized anxiety disorder
GMM: generalized mixed model
HF-ACTION: Heart Failure: A Controlled Trial Investigating Outcomes of Exercise Training
hsCRP: high sensitivity C-reactive protein
IQR: interquartile range
I-START: Internet-Based Strategic Transdisciplinary Approach to Risk Reduction and Treatment
KCCQ: Kansas City Cardiomyopathy Questionnaire
LMM: linear mixed models
LVEF: left ventricular ejection fraction
MI: motivational interviewing
MPR: medication possession ratio
NT-proBNP: N-terminal pro-brain natriuretic peptide
NYHA: New York Heart Association
PASE: Physical Activity Scale for the Elderly
PHQ-9: Patient Health Questionnaire
PSS: Perceived Stress Scale
REACH: Promotes Blood Pressure Reduction and Therapeutic Lifestyle Change in Hypertension
RR: relative risk
SHFM: Seattle Heart Failure Model
UHN: University Health Network

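### The outcome section names BNP as the peptide taken from charts, while the hypothesis and the analysis model test NT-proBNP

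*Protocol article*

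**What the plan says.** Four places in the protocol article bear on this.

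- **Secondary Hypotheses.** Among the prognostic measures expected to fall by 12 months in the e-Counseling arm is "N-terminal pro-brain natriuretic peptide (NT-proBNP").
- **Secondary Outcomes.** The paragraph on this marker speaks only of BNP. It opens with "The brain natriuretic peptide (BNP) is a neurohormone that is synthesized in and secreted from the ventricular myocardium" and justifies the choice with "BNP is increased in patients with CHF [89], and it correlates with risk for all-cause, cardiac, and pump-failure mortality". After a sentence on hsCRP it gives the data source: "We will extract these data, if available, from the medical charts of subjects at the baseline and 12-month assessments".
- **Statistical Analysis.** A linear mixed model with a random intercept compares the groups on "improvement at the 12-month interval in VO_2_ peak, NT-proBNP, hsCRP, and the SHFM". BNP is not an analysis variable.
- **Abbreviations.** The entry "BNP: brain natriuretic peptide" stands apart from a second entry for NT-proBNP.

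**The concern.** The variable that is hypothesised and modelled is not the one named where collection is described. A chart extractor working from the outcome section would look for BNP; an analyst working from the analysis section needs NT-proBNP. The article names no trial assay or central laboratory, and availability depends on what each of three hospitals happened to measure. Charts may therefore hold either peptide.

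Two harms could follow if both analytes entered one model. First, a scale difference between hospitals would add noise; neither site nor analyte is among the predictors listed for continuous secondary outcomes. Second, if a subject had one analyte at baseline and the other at 12 months, the difference in scale would appear as a change in the marker, and adjusting for the baseline value could not repair that.

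**Working it through.** **Comparing the text.** There is no planned figure to reproduce: the sample size section rests on the KCCQ responder outcome alone, and no calculation was made for this marker. Set side by side:

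- Hypothesis: NT-proBNP.
- Outcome description and stated chart source: BNP.
- Model: NT-proBNP.
- Abbreviation list: two separate terms.

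No sentence links the two names or says what to do when a chart holds only one of them.

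**How much a mixture would cost.** The article gives no figures, so every input here is an assumption:

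- one site in three reports the other analyte, always the same one at that site;
- the two analytes differ by a factor k of 3 to 8;
- the SD on the log scale within an analyte is 1, so the variance is 1;
- the correlation r between baseline and 12-month log values is 0.5 to 0.7.

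Step 1. The variance that the site offset adds to each visit is d = (ln k)² × (1/3) × (2/3).

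- k = 3: d = (1.0986)² × 2/9 = 0.268
- k = 8: d = (2.0794)² × 2/9 = 0.961

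Step 2. The offset is the same at both visits, so it enters the covariance as well as the variances. Each variance becomes 1 + d and the covariance r + d. The residual variance after adjusting for baseline is (1 + d) − (r + d)²/(1 + d), which equals (1 − r)(1 + r + 2d)/(1 + d). Without a mixture (d = 0) it is 1 − r².

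- r = 0.7, no mixture: 0.510. With k = 3: 0.3 × 2.236/1.268 = 0.529, a rise of 4%. With k = 8: 0.3 × 3.622/1.961 = 0.554, a rise of 9%.
- r = 0.5, no mixture: 0.750. With k = 3: 0.5 × 2.036/1.268 = 0.803, a rise of 7%. With k = 8: 0.5 × 3.422/1.961 = 0.873, a rise of 16%.

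Step 3. If the analyte switches within a subject, that subject's log change shifts by ln k, which is 1.10 to 2.08 under the same range for k, against an assumed SD of 1. The article gives no basis for estimating how often this would occur.

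**Direction.** The abstract states that randomisation is in blocks within each site, and Randomization and Blinding gives balance across sites as the purpose. A site-level difference in analyte is therefore expected to fall equally on both arms, so the cost is precision and not a systematic difference between arms.

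**The case against.** The strongest reply is that BNP in the outcome section is simply loose wording for the NT-proBNP named in both the hypothesis and the model. The sentence that names it is background physiology, and the extraction sentence excludes nothing. The abstract assigns prognostic indicators of cardiovascular functioning to chart review, and the hypotheses list NT-proBNP among the prognostic measures; read together, these make NT-proBNP a chart-review variable. This reading is plausible and cannot be ruled out. It limits the consequence but does not remove the inconsistency, because the outcome section would still name the wrong analyte to the extractor.

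A reader might infer that the comparison must have either no matching data or a mixture of two assays. The article does not support that, because the loose-wording reading is a third possibility and nothing shows which assays the hospitals use.

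A reader might also take the unadjusted figures in step 1, a rise of 27% to 96% on a variance of 1, as the cost. That overstates it: the analysis section lists the baseline value among the predictors for continuous secondary outcomes. The sentence on NT-proBNP does not repeat that list, but an analysis of change would likewise cancel an offset common to both visits.

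It is fair, too, that extraction-form details usually belong in a fuller document. Their absence is not the finding here; the finding is that the article states two different analytes for one outcome.

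**Conclusion.** The inconsistency is real and is established by the text alone. Its consequence is a risk that depends on what the charts contain. If each site uses one analyte consistently, the expected harm is a modest loss of precision: about 4% to 16% more residual variance, conditional on the assumed one-in-three mix, 3- to 8-fold scale difference, log-SD of 1 and correlation of 0.5 to 0.7. If analytes switch within subjects, spurious changes would arise, at a frequency the article gives no means of judging. The severity is minor: one opportunistically collected secondary prognostic marker is affected, and the primary outcome and the sample size are not.

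**What to change.** - Name the same analyte in Secondary Hypotheses, Secondary Outcomes and Statistical Analysis.
- Record with every chart value which peptide it is.
- Use a subject in this analysis only when the baseline and 12-month values are the same analyte.
- Do not pool BNP and NT-proBNP in one model.
- Include site as a predictor, since randomisation is already done within site.

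The cost is a wording change, one field on the extraction form and one model term, best settled before extraction begins. The downside is that subjects whose charts hold only the other analyte leave this secondary analysis, which further reduces a sample already limited to what the charts contain.

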**Methods:**

Canadian e-Platform to Promote Behavioral Self-Management in Chronic Heart Failure (CHF-CePPORT) is a multi-site, double blind, randomized controlled trial with a 2 parallel-group (e-Counseling + Usual Care vs e-Info Control + Usual Care) by 3 assessments (baseline, 4-, and 12-month) design. We will identify subjects with New York Heart Association Class II or III systolic heart failure from collaborating CHF clinics and then recruit them (n=278) by phone. Subjects will be randomized in blocks within each site (Toronto, Montreal, and Vancouver). The primary outcome will be improved quality of life, defined as an increased number of subjects with an improvement of ≥5 points on the summary score of the Kansas City Cardiomyopathy Questionnaire. We will also assess the following secondary outcomes: (1) diet habits, depression, anxiety, smoking history, stress level, and readiness for change using self-report questionnaires, (2) physical activity level, current smoking status, and vagal-heart rate modulation by physiological tests, and (3) exercise capacity, prognostic indicators of cardiovascular functioning, and medication adherence through medical chart review. The primary outcome will be analyzed using generalized estimation equations with repeated measures on an intention-to-treat basis. Secondary outcomes will be analyzed using repeated-measures linear mixed models with a random effects intercept. All significant main effects or interactions in the statistical models will be followed up with post hoc contrasts using a Bonferroni correction with a 2-sided statistical significance criterion of *P*<.05.

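### VO2 peak, NT-proBNP and hsCRP are tested as 12-month hypotheses but taken from routine charts, so clinical test-ordering after randomisation decides who is compared and the tests cannot reliably support the hypotheses

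*Protocol article*

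**What the plan says.** Secondary Hypotheses predicts that the e-Counseling arm "will perform better than the Control groups at the 12-month assessment on the following prognostic measures of cardiovascular functioning". The list includes lower NT-proBNP and hsCRP, a lower Seattle Heart Failure Model (SHFM) score, and "increased VO_2_ peak [55] during cardiopulmonary exercise testing". Statistical Analysis plans a linear mixed model with a random intercept to evaluate whether e-Counseling versus Control "demonstrates improvement at the 12-month interval in VO_2_ peak, NT-proBNP, hsCRP, and the SHFM".

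Secondary Outcomes gives the source of the values. For VO2 peak: "We will be collecting this information on the subjects through medical chart review". For the natriuretic peptide (called BNP in that paragraph) and hsCRP: "We will extract these data, if available, from the medical charts of subjects at the baseline and 12-month assessments". The Abstract agrees, listing "exercise capacity, prognostic indicators of cardiovascular functioning, and medication adherence through medical chart review". The SHFM inputs are also extracted from charts.

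The only missing-data rule shown is in Statistical Analysis: "Data missing at random will be handled by multiple imputations". By contrast, the 6-minute walk test (6MWT) is performed for the trial at baseline and 12 months and expressed as percent predicted. It is among the 12-month hypotheses but is not named in the 12-month model sentence.

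**The concern.** A randomised comparison is protected because both arms are measured in the same way. Here a 12-month value exists only if someone in routine care ordered the test after randomisation. The entry criteria select stable patients on stable treatment, so later testing may well respond to clinical course, and clinical course is what the intervention is meant to change. The arms actually compared would then be subsets formed after randomisation.

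A mixed model fitted to the observed values, and imputation under missing at random, are valid only if missingness is explained by what the model contains. For the continuous outcomes the listed predictors are the baseline value, age, sex, body mass index, time and group. The events that lead a clinician to order a test are not among them.

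At stake is a claim, with P values, of better prognostic cardiovascular measures. The Discussion expects the trial's data to help develop a Phase 3 trial.

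**Working it through.** The plan gives no figure for how many subjects will have a chart value, so the size of the problem can only be shown as a range.

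**Inputs from Sample Size Estimation**
- VO2 peak gain in the cited exercise-training trial: 0.6 (IQR −0.7 to 2.3) with exercise and 0.2 (IQR −1.2 to 1.4) in controls, in ml/kg/min. The plan expects a similar small change, so the expected difference is 0.6 − 0.2 = 0.4.
- SD, assuming a normal shape: IQR/1.349 gives 3.0/1.349 = 2.22 and 2.6/1.349 = 1.93. Pooled: √[(2.22² + 1.93²)/2] = 2.08.

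**Assumptions (not in the document)**
- No true effect: change Y ~ N(0, 2.08²) in both arms.
- The chance of having a 12-month test is p_d in subjects who fall by more than 1 ml/kg/min and p_r in the rest. The reference arm has p_d = 0.60 and p_r = 0.30.

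**Formula**
- Share of decliners: q = Φ(−1/2.08) = 0.315.
- c = 2.08 × φ(1/2.08) = 0.739.
- Mean among tested subjects = c(p_r − p_d) / [q·p_d + (1 − q)·p_r].
- Reference arm: 0.739 × (−0.30) / 0.395 = −0.56.

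| Other arm (p_d / p_r) | Mean in tested | Spurious difference |
|---|---|---|
| 0.60 / 0.30 (identical) | −0.56 | 0 |
| 0.75 / 0.375 (proportional rise) | −0.56 | 0 |
| 0.70 / 0.40 (0.10 added to both) | −0.45 | 0.11 |
| 0.60 / 0.40 (rise in non-decliners only) | −0.32 | 0.24 |
| 0.60 / 0.50 (rise in non-decliners only) | −0.14 | 0.42 |

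Against the expected 0.4, the artefact is therefore nil in some cases and as large as the effect in others.

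**Second check, different mechanism.** Let the log-odds of having a result be linear in the outcome, with half of 115 per group available and no true effect.
- Same slope in both arms: bias 0, type I error 0.05.
- Slopes of 0.5 and 0.2 per SD: bias 0.14 SD, type I error 0.11.
- Slopes of 0.7 and 0.2: 0.22 SD and 0.21.
- Slopes of 1.0 and 0 (extreme): 0.41 SD and 0.60.

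With a true effect of 0.3 SD and the same selection rule in both arms, the observed effect shrinks only modestly, to 0.29, 0.27 and 0.25 SD for slopes of 0.3, 0.7 and 1.0.

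Both checks agree: bias under the null needs selection that differs by arm.

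**The case against.** The strongest reply is that nothing in the article shows selection differing by arm.

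- **Ordering rule.** The article does not say when these tests are ordered. That worsening prompts them is an inference, and testing in tertiary heart-failure clinics may be largely periodic.
- **Blinding.** The cardiologists who identify patients are coinvestigators, and Randomization and Blinding says the research team will not know assignment. That closes the route through knowledge of arm and leaves the indirect route through clinical course.
- **Message content.** A reader might infer that e-messages in both arms promote appointments and symptom monitoring, and so change testing. Only the Control Group section describes such content. The e-Counseling section speaks of tools for self-monitoring of self-care. The text therefore gives no basis for assuming that e-Counseling raises testing.
- **VO2 peak wording.** The proviso about availability is written for the biomarkers only. VO2 peak is said to come from chart review without it.
- **Missing data.** The imputation sentence follows the binary-outcome model and does not declare every absent chart value missing at random. Further handling may sit in a document that is not shown.

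All of this stands, and it limits the point to a risk of unknown size. It does not remove the point. The chart source and the formal between-arm tests are both stated design choices, and no scheduled test is described that would make availability independent of care after randomisation.

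**Conclusion.** The point holds in a limited form. The 12-month comparisons of VO2 peak, NT-proBNP and hsCRP cannot reliably support the stated hypotheses, because clinical ordering after randomisation fixes who has a value and neither the mixed model nor imputation under missing at random repairs that.

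For VO2 peak the illustrative bias runs from 0 to about 0.4 ml/kg/min against an expected difference of about 0.4. These are results of assumed testing probabilities, a normal shape and no true effect. They are neither estimates nor bounds. No figure can be given for the biomarkers.

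Two stronger readings are not supported:
- That the comparison cannot answer the hypotheses at all. With identical or proportional selection in both arms and no effect, the test keeps its size. The article simply offers no way to check that case.
- That low power is a further defect. Even with values for all 115 per group, power for a 0.4 difference is only about 0.31, but the trial was sized on KCCQ responders and not on this secondary measure.

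The primary KCCQ outcome is not affected.

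**What to change.** 1. In Secondary Hypotheses and Statistical Analysis, label the chart-derived VO2 peak, NT-proBNP and hsCRP comparisons as exploratory. Do the same for the SHFM where its 12-month inputs depend on the same chart availability. The VE/VCO2 slope is in neither the hypotheses nor the model sentence and needs no change there.
2. Report the number and percent of subjects with a value, by arm, within a fixed window around baseline and 12 months.
3. Do not rely on missing-at-random imputation alone for these measures. Add a sensitivity analysis for values not missing at random.
4. Name the 6MWT (percent predicted) in the 12-month mixed-model sentence as the measure that carries the exercise-capacity hypothesis.

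The cost is wording and the loss of firm inferential claims on these chart-based secondary measures. No extra tests, visits or patients are needed.
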